##### 7.3.3. Post treatment

Repeated measures analysis of variance (ANOVA) will be performed on continuous variables (see Section 5), comparing the results obtained between baseline and ATMX, baseline and Placebo, and between ATMX and Placebo. Cohen's d effect size will be calculated using the mean differences between baseline and ATMX, and baseline and Placebo. Analyses will be performed in the total cohort, and then comparing those with and without comorbid anxiety. Presence/absence of previous stimulant treatment for ADHD, and an interaction term between presence/absence of comorbid anxiety and previous stimulant treatment will be used as covariates.

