The findings from the ACTION study will help support a more personalized approach to treatment options available for children and adolescents with ADHD by examining the efficacy of ATMX in improving both subjectively-rated symptom measures and objectively-assessed performance in ADHD. It will also provide evidence about which objective cognitive markers relate to ATMX response in ADHD, and how anxiety moderates ATMX response. An evidence-base of this kind may help support clinicians in making decisions about if and when to consider non-stimulants as an alternative to stimulants or non-pharmacologic treatments in each individual child or adolescent.

The primary aims of the ACTION study are to:

1. Assess whether ATMX has efficacy in improving cognition and emotional function in children and adolescents with ADHD.

2. Assess whether presence of co-morbid anxiety influences the response to ATMX in children and adolescents with ADHD in relation to cognition and emotional function.

3. Ascertain the reliability of cognitive and emotional function changes after ATMX compared to clinical symptoms of ADHD, and how these correlate with symptom changes. Please refer to Section 5 for more detail.

The methodology for the ACTION study will be detailed in this manuscript.

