### 5. Research endpoints

The primary endpoint will be clinically significant improvement in cognition and emotional function after ATMX treatment assessed using IntegNeuro™ (Table 1); and in ADHD symptoms (ADHD-RS IV, CGI, WPREMB, and CPRS-R subscales: Cognitive problems/inattention, Hyperactivity, Conners' ADHD index, CGI restless-impulsive, CGI total, DSM-IV inattentive, DSM-IV hyperactive-impulsive, and DSM-IV total). Further analyses will be undertaken to compare the differences in ATMX treatment effects between participants with and without comorbid anxiety; and between ADHD subtypes.

Part of the novelty of this trial lies in our utilization of objective assessments for cognition and emotional function. As such, we will also determine if our objective measures predict response to ATMX in ADHD, and in patients with comorbid anxiety. Treatment response is defined in Section 7.3.2.

The secondary endpoints will be improvements after ATMX treatment in quality of life (PedsQL - self and parent); emotional states and self-regulation (DASS-BRISC); and state and trait anxiety (CPRS-R subscales: Anxious-shy, STAI and STAIC). Previous ADHD treatment with stimulant medication and comorbid anxiety will be included as covariates.

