### 7. Statistical analysis

#### 7.1. Sample size

The data used for the power calculation of the inhibition function primary outcome measures are from a sample of 175 ADHD individuals assessed off and then on stimulant medication (methylphenidate or dexamphetamine; data not published). The power calculation of the emotional function primary outcome measures are based on a sample of 30 ADHD participants from the same sample.

Power was set at 0.9, alpha level at 0.05, and the mean difference (change in off-versus on-medication) and standard deviations for the mean of the n = 175 group was used. The means for the n = 30 group were set at '0', since there was no change expected in these outcome measures for the placebo group. After applying the pilot data means from each primary outcome measure the highest sample size estimate we obtained was n = 152 for each group under two-tailed conditions. Therefore, a minimum total of 152 participants are required in this cross-over study to achieve the desired level of probability in detecting a statistically significant difference across the two primary outcome measures.

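### Section 7.3.3 names an anxiety by previous-stimulant interaction but never the treatment by anxiety term through which primary Aim 2 would be tested

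*Protocol article*

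**What the plan says.** The second primary aim (protocol article, Background) is to "Assess whether presence of co-morbid anxiety influences the response to ATMX in children and adolescents with ADHD in relation to cognition and emotional function". Section 5, Research endpoints, restates it as an analysis: to "compare the differences in ATMX treatment effects between participants with and without comorbid anxiety".

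Section 7.3.3, Post treatment, is where the model for continuous outcomes is fixed. It specifies repeated measures ANOVA for baseline versus atomoxetine, baseline versus placebo, and atomoxetine versus placebo. On anxiety it says: "Analyses will be performed in the total cohort, and then comparing those with and without comorbid anxiety". It then lists the presence or absence of previous stimulant treatment as a covariate, and adds that "an interaction term between presence/absence of comorbid anxiety and previous stimulant treatment will be used as covariates".

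Section 5 gives a different covariate list, at the end of its paragraph on secondary endpoints: "Previous ADHD treatment with stimulant medication and comorbid anxiety will be included as covariates". The anxiety main effect is on that list but not on the list in 7.3.3. The product term is in 7.3.3 but not in Section 5.

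**The concern.** Whether anxiety changes the response to a drug is a question about a treatment by anxiety interaction. The one interaction that 7.3.3 names is between two fixed characteristics of the child, so on its own it says nothing about treatment. The term that Aim 2 needs is left to be inferred from a sentence that an analyst could also carry out as one ANOVA in anxious children, another in non-anxious children, and a comparison of the two p-values.

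At stake is a primary aim. Depending on how the analyst reads the section and how the software handles covariates, the Aim 2 result could be a proper interaction test, an interaction test restricted to part of the sample, or an informal comparison of subgroup significance.

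**Working it through.** **Inputs from the document.** Total N = 152, two-sided alpha 0.05, power 0.9 (Section 7.1).

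**Inputs assumed, because the document does not give them.** Share with anxiety 20-50%; share with prior stimulant treatment 30-70%; within-child correlation 0.6; an atomoxetine effect 0.5 SD larger in anxious children (SD of the outcome).

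**The plan's own figure.** The 152 cannot be reproduced, since neither the mean difference nor the SD is printed. Solving backwards with 1.960 + 1.282 = 3.242:
- as n per group: √2 × 3.242 / √152 = 0.372 SD;
- as a paired total: 3.242 / √152 = 0.263 SD of the within-child difference.

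**Reading 1: the product enters additively.** Write the outcome of child i under condition j as a child effect + treatment effect + b₁·stimulant + b₂·(anxiety × stimulant) + error. The two covariate terms are the same under both conditions, so they cancel from the atomoxetine-placebo difference. A complete-data check gave a treatment estimate of 0.21555 with and without the covariates.

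**Reading 2: covariates are crossed with condition**, as general-linear-model repeated measures ANOVA commonly does, with anxiety as the between-child factor. For the atomoxetine-placebo difference D:

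D = t + g₁·anxiety + g₂·stimulant + g₃·(anxiety × stimulant) + error

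With uncentred 0/1 coding, g₁ is the anxiety contrast among children with no prior stimulant treatment only.

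- SD of D = √(2 × (1 − 0.6)) = 0.894.
- Without the product, 30% anxious: 45.6 and 106.4 children; SE = 0.894 × √(1/45.6 + 1/106.4) = 0.158; 0.5/0.158 = 3.16; power = Φ(3.16 − 1.96) = 88% (87% by simulation).
- With the product, half with prior stimulants: 22.8 and 53.2 children; SE = 0.894 × √(1/22.8 + 1/53.2) = 0.224; 0.5/0.224 = 2.23; power = Φ(2.23 − 1.96) = 61% (60% by simulation).
- Over 20-50% anxious and 30-70% with prior stimulants, simulated power is 76-93% without the product and 32-81% with it.

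The loss depends on the coding. If the stimulant indicator is centred at its share q, the anxiety coefficient becomes a (1 − q) and q weighted average of the contrasts in the two stimulant strata. Its variance is then about the same as without the product, and the loss disappears.

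**Reading 3: separate subgroup ANOVAs.** Suppose the true effect is the same in both groups, at the back-solved 0.263 SD of the within-child difference. With 30% anxious, the power is Φ(0.263 × √45.6 − 1.96) = 43% in anxious children and Φ(0.263 × √106.4 − 1.96) = 77% in the others. The chance that exactly one is significant is 0.43 × 0.23 + 0.57 × 0.77 = 54% (55% by simulation). Simulation gives 63% at 20% anxious and 47% at 50%. The formal interaction test rejects in 5-6%. With a true effect of 0.5 SD the discordance falls to 25%, 8% and 2% at 20%, 30% and 50% anxious.

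**The case against.** The strongest reply is that the plan already contains the right comparison. Section 5 plans to compare treatment effects between anxiety groups, which in substance is the interaction. Section 7.3.3 carries that into the ANOVA, where anxiety as a between-child factor yields the condition by anxiety test. The stimulant product is listed only as a covariate. This is also a journal article, and exact model terms are commonly left to the analysis plan.

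Much of this stands, and it rules out two stronger readings.

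- A reader might infer that the plan does not test Aim 2 at all, or tests the stimulant product in its place. The documents do not support that: the intended comparison is stated in Section 5 and again in 7.3.3.
- A reader might note that, without an anxiety main effect, the product can be significant merely because anxious and non-anxious children differ in level (59-65% of simulated trials with a 0.5 SD level difference), and call this a false Aim 2 finding. Nothing in the protocol says that the product's p-value answers Aim 2. Section 5 lists anxiety as a covariate, and in 7.3.3 anxiety may already be the grouping factor.

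The cancellation in Reading 1 also holds only for an additive model with complete data. Section 7.3 plans to use all available data without imputation, so exact identity in the real data is not guaranteed.

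What does not stand is the appeal to the analysis plan. The article did not stay silent on interactions: it fixed one, and the one it fixed does not serve the aim.

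**Conclusion.** The point holds as a fault in how the model is fixed. The aim and Section 5 are worded correctly, but 7.3.3 names an interaction that does not inform Aim 2 and omits the one that does. It also leaves open whether the anxiety comparison is a formal contrast or a set of subgroup analyses.

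The consequence depends on the reading. Entered additively with complete data, the product does nothing to the atomoxetine-placebo contrast. Crossed with condition under uncentred 0/1 coding, it narrows the anxiety test to children without prior stimulants and costs power, for example 87% down to 60%. Read as separate subgroup analyses, a comparison of p-values would suggest a difference between the groups in roughly half of trials or more when none exists, if the true effect is near 0.263 SD, and far less often if it is larger.

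The algebra follows from the terms named in 7.3.3. The power figures rest on the assumed anxiety share, stimulant share, correlation and moderation size. The correlation and moderation size were not varied, so these figures illustrate the loss and do not predict it.

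**What to change.** In Section 7.3.3, replace the anxiety by previous-stimulant term with a treatment by anxiety term plus the anxiety main effect. State that the Aim 2 test is one estimate, the difference between anxiety groups in the atomoxetine-placebo effect, reported with its 95% CI. State also that subgroup p-values will not be compared. If prior stimulant use may confound the moderation, add treatment by previous stimulant. Use the same covariate list in Sections 5 and 7.3.3.

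The cost is wording only, since anxiety status and previous stimulant treatment are already planned variables. The fix makes the test clear but does not make it strong. With 152 children, the interaction detectable with 90% power is 0.66, 0.57, 0.54 or 0.53 SD of the within-child difference at 20%, 30%, 40% or 50% anxious. An interaction of 0.263 SD would be detected with 25-37% power. The confidence interval should therefore carry the interpretation.

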## Results and Discussion

The ACTION study will be a multi-site, double-blinded, randomized cross-over study examining the effects of ATMX on cognitive and emotional functions in children and adolescents with ADHD, whilst also identifying objective predictors of ATMX response in this group, including those with and without comorbid anxiety. The cross-over design of the study enables participants to act as their own controls when testing whether cognitive and emotional function at baseline is able to predict changes in symptom ratings after medication treatment. Enrolment and testing commenced in March 2008. Potential limitations in the study design pertain to the one-week washout period between treatment phases, and the absence of an "anxiety only" arm for examining comorbid anxiety outcomes. Although our selection of a washout period of one-week's duration was based on previous research [53-55], it is not known if any carry over effects were present. However, it is highly unlikely that the results obtained after six weeks of placebo treatment could be attributed to ATMX in those participants receiving active treatment (ATMX) in Phase A. Future studies may consider observing changes at first response and full response, and to vary the length of their washout periods between treatments. Additionally, an anxiety only arm should also be incorporated if investigating changes in comorbid anxiety outcomes.

## Conclusions

The detailed methodology for the ACTION study has been presented. The novelty of this trial lies in its utilization of objective measures for cognition and emotion; and in its combination of objective and subjective, commonly-used assessment tools to determine the efficacy of ATMX in ADHD with and without comorbid anxiety. This research will further our knowledge on the effective use of ATMX in improving symptoms in child and adolescent ADHD; providing additional evidence to aid in personalized treatment approaches.

## Abbreviations

ACTION: ADHD Controlled Trial Investigation Of a Non-stimulant; ADISC: Anxiety Disorders Interview Schedule for DSM-IV: Child version (Parent interview schedule); ADHD: Attention Deficit Hyperactivity Disorder; ADHD-RS IV: Attention Deficit Hyperactivity Disorder - Rating Scale IV; ANOVA: Analysis Of Variance; ATMX: Atomoxetine; BRISC: Brain Resource Inventory of Social Cognition; CCTV: Closed Circuit Television; CFR: Code of Federal Regulations; CGI: Clinical global impression scale; CHW: Children's Hospital at Westmead; CPRS-R: Conners' parent rating scale - revised (long version); CTCs: Clinical trial coordinators; DASS: Depression; anxiety and stress scale; DSM-IV: Diagnostic and Statistical Manual of Mental Disorders - Fourth edition; FDA: U.S. Food and Drug Administration; ICH: International Conference on Harmonization; ID: Identification; PedsQL: Pediatric quality of life inventory; STAI: State-trait anxiety inventory; STAI-C: State-trait anxiety inventory for children; WPREMB-R: Weekly parent rating of evening and morning behavior - revised.
